**3. BRIEF PROTOCOL SUMMARY**

|                             |                                                                                                                                                                                                                                                                                                                                                                                                                                                                                                                                        |
|-----------------------------|----------------------------------------------------------------------------------------------------------------------------------------------------------------------------------------------------------------------------------------------------------------------------------------------------------------------------------------------------------------------------------------------------------------------------------------------------------------------------------------------------------------------------------------|
| Short Title          | TEXT-PAD study                                                                                                                                                                                                                                                                                                                                                                                                                                                                                                                         |
| Protocol Version     | Version 1.6                                                                                                                                                                                                                                                                                                                                                                                                                                                                                                                            |
| Protocol Date        | 19/03/2021                                                                                                                                                                                                                                                                                                                                                                                                                                                                                                                             |
| Funding Source       | League of friends of freeman hospital and departmental funding                                                                                                                                                                                                                                                                                                                                                                                                                                                                         |
| Study design         | Feasibility study and pilot randomised control trial with embedded process evaluation                                                                                                                                                                                                                                                                                                                                                                                                                                                  |
| Study Intervention   | A 12-week home-based telehealth behavioural intervention delivered in low SES patients with PAD                                                                                                                                                                                                                                                                                                                                                                                                                                        |
| Primary objectives   | To assess the feasibility and acceptability of a 12-week home-based telehealth behavioural intervention delivered in low SES patients with PAD                                                                                                                                                                                                                                                                                                                                                                                         |
| Secondary objectives | 
 
1. To determine the preliminary effectiveness of a 12-week home-based telehealth behavioural intervention compared to usual care, including effect on: functional status, tobacco and alcohol use, quality of life, dietary quality, mental wellbeing and daily ambulatory physical activity levels
 
2. To develop and test tools to measure the costs and effects for the health economic evaluation of 12-week telehealth behavioural intervention compared to usual care.
 
 |
| Study site           | Single centre study – Newcastle upon Tyne NHS trust                                                                                                                                                                                                                                                                                                                                                                                                                                                                                    |
| Study population     | Patients attending the vascular outpatient clinic at Freeman Hospital with a confirmed diagnosis of PAD and from lowest 30% of super-output areas                                                                                                                                                                                                                                                                                                                                                                                      |
| Study duration       | 12 months                                                                                                                                                                                                                                                                                                                                                                                                                                                                                                                              |
| Sponsor              | Newcastle upon Tyne NHS Trust                                                                                                                                                                                                                                                                                                                                                                                                                                                                                                          |

#### 4. **BACKGROUND**

Peripheral arterial disease (PAD) results from chronic atherosclerosis that progressively leads to partial or total obstruction of the arteries, thereby, reducing blood flow and oxygen delivery to the peripheral regions of the body (1). The main symptom of PAD is intermittent claudication, characterized by pain, cramp, or burning that occurs in the lower limbs during walking exercise and is relieved by rest (2). Due to these symptoms, patients with PAD experience lower physical function (3), impaired cardiovascular function and lower quality of life (4). Based on evidence demonstrating the benefits of exercise on walking capacity (5), cardiovascular function (6, 7) and quality of life (5), supervised exercise training is recommended by the National Institute for Health and Clinical Excellence (NICE) as first line treatment of claudication caused by PAD (8). NICE also recommends that patients with PAD are offered advice, support, and treatment for the secondary prevention of cardiovascular disease (CVD), including smoking cessation, diet, weight management, and exercise (8). Despite these recommendations, supervised exercise is rarely delivered in the clinical setting and, patients are not systematically offered evidence-based interventions that support behavioural modification. Ineffectual provision of and, referral to, behaviour change programmes may contribute to further deterioration of health, leading many patients to undergo surgical procedures for PAD management e.g. stent or bypass. While these procedures may provide short term benefits, they incur greater risk and cost (9, 10). Also, without comprehensive behavioural intervention, patients are likely to resume the same poor health behaviours that contributed to PAD development initially. Therefore, there is an imperative to develop, evaluate and integrate into care pathways ‘prehabilitation’ interventions that optimise patient health, prevent further deterioration and improve long-term outcomes. Given the systematic relationship between deprivation and health, these programmes are accessible and acceptable to socioeconomically deprived patients.

Usually, supervised exercise programmes and behavioural interventions are delivered face-to-face. However, the current covid-19 pandemic has significantly changed the organizational structure of health institutions and diverted attention to pandemic management (11). There has also been reports of outbreaks during exercise sessions, limiting face-to-face delivery of care to high-risk populations until a vaccine has been developed (12). Telephone-health (tele-health) enables patients to access care remotely via digital platforms. It represents a ‘COVID-proof’, cost-effective and scalable care delivery option (13) and mitigates some traditional barriers to access e.g. living remotely.

This pilot RCT will establish the feasibility and acceptability of a 12-week home-based telehealth exercise and behavioural intervention delivered in low SES patients with PAD. The programme will be developed and delivered collaboratively between Newcastle upon Tyne NHS Trust, Northumbria University, Newcastle University, Healthworks and Newcastle United Foundation Club (NUFC) Foundation. The use of premier football team branding has been shown to improve the effectiveness of exercise and weight loss interventions (12,13) and improve recruitment of ‘hard to engage’ men (14). This study will also determine the preliminary effectiveness of the intervention for improving clinical and health outcomes.

## **5. PRIMARY RESEARCH QUESTION**

Is it feasible to deliver a 12-week homebased multimodal telehealth behavioural intervention in low SES patients with PAD and, is the intervention and study acceptable to patients?

## **6. AIMS and OBJECTIVES OF THE STUDY**

### **6.1. Primary aim**

To investigate the feasibility and acceptability of a 12-week homebased multimodal telehealth behavioural intervention in low SES patients with PAD.

### **6.2. Primary objectives**

To determine:

- Rates of patient screening, eligibility, recruitment, and retention to 12-week follow-up
- Patient compliance to the intervention (number of sessions attended and completed)
- Patient acceptability of the intervention through semi-structured qualitative interviews

### **6.3. Secondary aims**

To determine the preliminary effectiveness of a 12-week homebased telehealth behavioural intervention compared to usual care.

### **6.4. Secondary objectives**

To investigate whether a 12-week homebased multimodal telehealth behavioural intervention compared to usual care:

- Improves functional capacity
- Reduces alcohol and tobacco use
- Improve diet quality
- Improves quality of life and mental wellbeing
- Increases daily ambulatory physical activity levels

### **6.5. Tertiary aim**

To explore the measurement of resource utilisation, costs and effects in an economic evaluation that would be conducted as part of a definitive RCT.

### **6.6. Tertiary objectives**

To develop and test tools to measure the costs and effects for the health economic evaluation of 12-week telehealth behavioural intervention compared to usual care.

## **7. STUDY DESIGN**

This is a single centred feasibility study and pilot randomised control trial assessing a 12-week telehealth behavioural intervention delivered in low SES patients with PAD. A logic model for this project is shown in Figure 1.

### **7.1. Participants**

Patient eligibility will be based on the criteria below.

#### *Inclusion criteria*

- Diagnosis of PAD confirmed by ankle brachial index  $<0.90$  in one or both limbs
- Age  $\geq 40$  years
- Able to walk distance  $>50\text{m}$
- Live in an area deemed in lowest 30% of super output area from Office of National Statistics

#### *Exclusion criteria*

- chronic limb threatening ischemia
- short claudication distance  $<50\text{m}$
- severe heart disease (Grade III or IV, New York Heart Association)

- severe ischemic or haemorrhagic stroke or neurodegenerative diseases
- severe hypertension (systolic blood pressure of more than 180 mm Hg, and a diastolic blood pressure of more than 100 mm Hg)
- uncontrolled cardiac arrhythmias (unstable angina during the previous month and myocardial infarction during the previous month)
- a resting heart rate of more than 120 beats per minute
- has already undergone angioplasty, bypass or other surgical intervention for PAD
- other severe comorbid conditions preventing the ability to engage in physical activity, inability or unwillingness to undertake the commitments of the study

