### *Supervised exercise*

The home-based exercise training will be performed twice a week for 12 weeks via Zoom (up to 5 patients per session). Each session will be comprised of warm-up (10 min), the main part (15 to 20 min), and cooldown (5 to 10 min). The training aim to develop resistance, aerobic and functional capacity such as getting up, walking, pulling, pushing, throwing, transferring body weight or external loads. An example of multimodal exercise training is shown in Box 1.

The training intensity will be progressively adjusted by increasing the load (e.g. using common household objects), increasing the complexity, speed of movements and volume of exercises by varying circuits. The intensity of the exercise will be monitored using the Borg scale (from 0 to 20) with target intensity zone from 12 to 14 (Somewhat hard to hard) (16).

In addition to the home-based training sessions, patients will be encouraged to increase their physical activity. Patients will be provided with a Fitbit device to monitor their step count and will be recommended to increase their previous week's average step count by 10%. Participants who have access to the internet will be asked to upload data to the Fitabase research platform. Data will be anonymised and will only be accessible to the research number.

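### The arrhythmia exclusion is defined by two ischaemic events joined by *and*, so label and bracket contradict each other; the joint blood-pressure rule needs its intent confirmed

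*Protocol*

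**What the plan says.** Section 7.1 of the protocol makes the criteria list decisive: "Patient eligibility will be based on the criteria below". Two of the exclusion bullets are at issue:

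- The arrhythmia bullet: "uncontrolled cardiac arrhythmias (unstable angina during the previous month and myocardial infarction during the previous month".
- The blood-pressure bullet: "severe hypertension (systolic blood pressure of more than 180 mm Hg, and a diastolic blood pressure of more than 100 mm Hg".

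Three other bullets in the same list could bear on the same patients: "severe heart disease (Grade III or IV, New York Heart Association", "a resting heart rate of more than 120 beats per minute" and "other severe comorbid conditions preventing the ability to engage in physical activity". Neither of the two bullets at issue is restated or corrected elsewhere in the protocol.

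On what participants then do, Section 8 (Supervised exercise) says of the intervention arm: "The home-based exercise training will be performed twice a week for 12 weeks via Zoom". Section 8.1 has the usual-care arm advised to walk for exercise without supervision. Section 9.2 has all patients perform a six-minute walk test. Sections 6.2, 9.1 and 11 list the rate of eligibility among the primary feasibility outcomes.

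**The concern.** A bracket after a diagnostic label normally tells the person screening what counts as that diagnosis. Here it does not: unstable angina and myocardial infarction are ischaemic events, and no rhythm disorder is listed. A screener who follows the label and one who follows the bracket are applying different rules.

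The connective adds a second difficulty. Taken as a logical *and*, the bracket is met only when both events fall in the previous month. The blood-pressure bullet uses the same connective between its systolic and diastolic limits.

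Two things are at stake. The list is a main stated safeguard for a trial that asks one arm to exercise at home under remote supervision and advises the other to walk unsupervised. In addition, the eligibility rate is itself a primary outcome. If the bullets can be read in more than one way, the count of eligible patients and the recorded reasons for exclusion depend on the reading chosen. Section 10 says the pilot will inform the power calculations of later definitive trials, so unclear criteria could also be carried forward.

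**Working it through.** No sample-size, power or error-rate figure is involved, so the check is one of wording and logic. Each bullet is treated as a condition that is met or not met, and is then compared with the rest of the list.

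**1. Arrhythmia bullet, label against bracket**

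The bracket column uses the literal, joint reading of *and*.

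| Patient | Meets the label? | Meets the bracket? | Result |
|---|---|---|---|
| Unstable angina and infarction, both in the previous month | Not by either event | Yes | Excluded if the bracket governs |
| Infarction in the previous month, no unstable angina | Not by that event | No | Not excluded by this bullet |
| Unstable angina in the previous month, no infarction | Not by that event | No | Not excluded by this bullet |
| Uncontrolled arrhythmia, neither event | Yes | No | Undefined |

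Rows 2 and 3 depend on taking *and* as joint. The mismatch in rows 1 and 4 does not: if *and* merely lists two separate items, the bracket still names no arrhythmia.

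**2. Blood-pressure bullet**

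The rule as written is: systolic above 180 mm Hg and diastolic above 100 mm Hg.

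| Pressure (mm Hg) | Systolic > 180? | Diastolic > 100? | Both, as written? |
|---|---|---|---|
| 185/105 | Yes | Yes | Met: excluded |
| 200/95 | Yes | No | Not met |
| 175/115 | No | Yes | Not met |

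This rule can be applied without ambiguity. What the protocol does not show is whether a joint condition was intended.

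**3. How the list uses its connectives**

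Elsewhere the list writes *or* where alternatives are meant, for example "severe ischemic or haemorrhagic stroke or neurodegenerative diseases". That gives a reader some ground for taking *and* as joint, but it does not settle the matter.

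**4. Whether another bullet closes the gap**

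- The New York Heart Association bullet tests functional grade. It does not mention recent infarction, unstable angina or blood pressure.
- The heart-rate bullet tests resting rate only. It would catch an arrhythmia only if the resting rate were above 120.
- The comorbidity bullet applies when a condition prevents physical activity, which is a judgement about ability and not a defined cardiac criterion.

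Each may exclude some of the patients in the two tables. None does so by naming the condition.

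**5. Number affected**

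The protocol gives no frequencies for recent infarction, unstable angina, arrhythmia or isolated high pressure in the screened population, so no count or percentage can be calculated.

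**The case against.** The strongest reply is that a clinician would understand what is meant. In the arrhythmia bracket the time window is repeated after each event, which suits a list of two separate items at least as well as a joint condition. The list is loosely drafted in other places too, so the contrast with *or* carries limited weight. This stands: the joint reading is the literal one but not the only one, and it would be too strong to say as fact that a patient with a recent infarction is eligible. It does not rescue the bullet, because under the list reading the label and the bracket still do not match.

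A reader might go further and infer that an uncontrolled arrhythmia without either event passes screening. The text does not support that. Such a patient meets the label, so the status is undefined and not eligible.

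A reader might also infer that the blood-pressure bullet contradicts itself, or was plainly meant to exclude 200/95 or 175/115. The protocol does not support that either. A joint threshold is a coherent definition, and the intent behind it is not stated.

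Finally, other steps narrow the gap. Besides the three bullets discussed above, Section 7.3 has the research team assess suitability and then see patients in hospital for consent and baseline. The study has a single centre, which limits variation between screeners. Feasibility rates are reported descriptively, so no decision threshold would be crossed by misclassifying a few patients. These points limit the consequence. They do not supply the missing definition.

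**Conclusion.** The arrhythmia bullet is wrong as written: its label and its bracket describe different conditions, however the connective is read. On the literal reading the bracket also requires two events together, which leaves infarction alone and unstable angina alone outside it. The blood-pressure bullet is not an error on its face; it is a question of intent that the sponsor should answer.

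The size in patients is unknown and cannot be derived from the protocol. The planned sample of 60 (30 per arm) and the analysis methods are unaffected. The effect falls on who may enter an exercise trial and on whether the eligibility rate can be reproduced. The conclusion assumes only that the bracket is meant to define or illustrate its label and that the list is applied as Section 7.1 says. It does not assume that any particular patient would be enrolled or harmed, and it takes no position on which clinical rule is right.

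**What to change.** The sponsor's clinical lead should:

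1. Reconcile the label and the bracket of the arrhythmia bullet, so that the text says which conditions it is meant to cover.
2. State, in both the arrhythmia and the blood-pressure bullets, whether each component excludes on its own or only together with the other.
3. Put the same wording on the screening form and log, so that eligibility and reasons for exclusion are counted under one rule.

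No threshold, time window or clinical rule is proposed here; those are for the clinical lead to decide. The cost is a wording amendment to two bullets and the matching change to the screening form. If screening has already begun, the log should record which reading was in use up to the amendment, so that the eligibility rate can be interpreted.

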### **7.3. Recruitment procedures**

A comprehensive list of patients with PAD attending the Freeman Hospital is already kept. The research team will assess potential suitability and contact the participants by telephone. If the participant expresses interest in the study the PIS and consent form will be forwarded on. Hospital visits will be undertaken for formal consent (baseline) and the follow-up outcome assessments.

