## **9. OUTCOME MEASUREMENTS**

### **9.1. Primary outcomes**

Feasibility will be determined by calculating the rate of patient screening, eligibility, recruitment, retention at 12 weeks and adherence to the intervention (number of sessions attended and completed).

Patient acceptability of the intervention and study experience more broadly will be determined through semi-structured qualitative 1-2-1 interviews and/or focus groups. Given the challenges of conducting focus groups remotely, and anticipated characteristics of the participant group, we expect that 1-2-1 interviews will be more practical and facilitative. We will purposively sample participants from both study arms so that the experiences of patients from varied ethnic backgrounds, age and gender are represented. Acceptability of the intervention will be guided by Sekhon et al.'s Theoretical Framework of Acceptability (17) and the NIH Behavior Change Consortium's Best Practices and Recommendations. We will also ask patients about their experience of participating in the study e.g. informed consent process, time commitment, acceptability of measures e.g. readability, burden etc. We will also ask for their experiences, thoughts and attitudes towards current usual care for PAD. Interviews will be conducted until data saturation is reached in a maximum of 20 participants.

All focus groups will be audio recorded and transcribed, and these data will be analysed thematically to generate themes and outcomes. Participants will receive a £20 voucher as reimbursement for their participation.

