## **11. DATA ANALYSIS**

Primary outcome data will be reported as descriptive statistics, including rates of: patient screening, eligibility, recruitment and retention to 12-week follow-up and survey completion. Qualitative interview data will be analysed thematically to generate themes. Exploratory between-group analyses will be conducted to determine preliminary intervention effectiveness. Normality and homogeneity of variance will be performed using the Shapiro-Wilks and Levene tests, respectively. For comparison of the variables at the pre-intervention, we will perform a one-way ANOVA. To analyze the responses before and after the intervention period, two-way analysis of variance for repeated measures will be used, with the main factors being the group (and the time (pre and post intervention) with Newman-Keuls post-hoc test. The level of significance will be set at  $P < 0.05$ .

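### Unwillingness to take on the study commitments is an exclusion criterion, so refusals can be counted as ineligibility and two primary feasibility rates are confounded

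*Protocol*

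**What the plan says.** Protocol section 7.1 opens with "Patient eligibility will be based on the criteria below". The last exclusion bullet joins two different things: severe comorbidity that prevents physical activity, and "inability or unwillingness to undertake the commitments of the study". The second is therefore part of the definition of eligibility.

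Eligibility and recruitment are named as separate primary quantities in three places:

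- The primary objectives, in section 6.2, list "Rates of patient screening, eligibility, recruitment, and retention to 12-week follow-up".
- The primary outcomes, in section 9.1, begin with "Feasibility will be determined by calculating the rate of patient screening, eligibility, recruitment, retention at 12 weeks and adherence to the intervention".
- The analysis text, in section 11, begins with "Primary outcome data will be reported as descriptive statistics, including rates of: patient screening, eligibility, recruitment and retention to 12-week follow-up and survey completion".

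None of the three gives a denominator for the recruitment rate.

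Section 7.3 sets the order of contact. First, "The research team will assess potential suitability and contact the participants by telephone". Then, "If the participant expresses interest in the study the PIS and consent form will be forwarded on". Section 7.4 makes participation voluntary and subject to signed consent.

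**The concern.** In a confirmatory trial a clause of this kind has little effect, because the analysis concerns outcomes after randomisation. Here the primary question is whether the programme and study are feasible and acceptable in low-SES patients, and willingness to take on the commitments is a large part of the answer. Those commitments are substantial: a one-hour health-trainer contact each week for 12 weeks and two Zoom exercise sessions a week (section 8), Fitbit wear every day (section 9.2), and hospital visits at baseline and follow-up (section 7.3).

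Willingness is what the recruitment rate ought to measure, yet the protocol also uses it to define eligibility. One telephone refusal can be logged as eligible but not recruited, or as excluded. The choice moves that patient between two primary outcomes. A definitive trial planned on the resulting recruited/eligible figure could expect better uptake than it will get.

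**Working it through.** The protocol states no screening, eligibility or uptake figure, so there is none to reproduce. The check asks how far the clause can move each rate.

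**Inputs**

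- R = 60 recruited, the target in section 10. It cancels out of the rates.
- u = true uptake among patients who meet all the other criteria (called clinically eligible below). Not in the protocol; assumed 20% to 70%.
- f = share of decliners coded ineligible under the clause. Not in the protocol; taken from 0 to 1.
- Share of screened patients who are clinically eligible. Not in the protocol; assumed 50%, and used only for the rates per patient screened.

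**Formulas**

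- Clinically eligible: E = R/u.
- Recorded as eligible: E′ = E − f(E − R).
- Recruited/eligible as recorded: R/E′ = u/[u + (1 − f)(1 − u)].
- Recruited/screened: R/S, where S is the number screened. This does not contain f.

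**Worked line.** Take u = 20%, f = 0.5. E = 60/0.20 = 300, so there are 240 decliners. E′ = 300 − 0.5 × 240 = 180. Recruited/eligible = 60/180 = 33%. By the formula, 0.2/(0.2 + 0.5 × 0.8) = 0.2/0.6 = 33%.

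**Recruited/eligible as recorded**

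| True uptake u | E | f = 0 | f = 0.5 | f = 0.9 | f = 1 |
|---|---|---|---|---|---|
| 20% | 300 | 20% | 33% | 71% | 100% |
| 30% | 200 | 30% | 46% | 81% | 100% |
| 50% | 120 | 50% | 67% | 91% | 100% |
| 70% | 86 | 70% | 82% | 96% | 100% |

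**Rates per patient screened, at the assumed 50% clinical eligibility**

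| True uptake u | Eligible/screened, f = 0 | f = 0.5 | f = 1 | Recruited/screened, any f |
|---|---|---|---|---|
| 20% | 50% | 30% | 10% | 10% |
| 30% | 50% | 32.5% | 15% | 15% |
| 50% | 50% | 37.5% | 25% | 25% |
| 70% | 50% | 42.5% | 35% | 35% |

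The second table shows where the refusals go. They do not vanish: they leave the recruitment rate and appear as ineligibility. With f unknown, neither rate can be interpreted alone.

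**Consequence for planning.** At u = 20% and f = 0.5, a planner reading 33% would budget 1/0.333 = 3 clinically eligible patients per recruit, when 1/0.20 = 5 are needed.

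**The case against.** The strongest reply is that the protocol never says decliners are ineligible. Section 7.3 has the team judge potential suitability from an existing list and establish interest only afterwards, on the telephone. A natural log entry is then suitable but declined. Some patients will also decline for reasons other than the commitments, such as reluctance to be randomised, and the clause does not cover them. Denominators and log coding are commonly left to a statistical analysis plan, which is not at hand. Retention, adherence and the acceptability interviews are measured after entry and are untouched. Unwilling patients would not be enrolled with or without the clause.

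Most of this stands, and it limits the size of the problem: f need not be near 1. It does not remove the problem. Potential suitability judged from a list is not eligibility under section 7.1, and a refusal on account of the commitments meets the last exclusion literally. An analysis plan can choose denominators, but it cannot make a patient who meets a protocol exclusion eligible. At best, two members of staff could log the same refusal differently.

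A reader might also infer that the clause shuts out low-SES patients without internet. The text does not support that. The sentence "Participants who have access to the internet will be asked to upload data to the Fitabase research platform" concerns Fitbit uploads by people already enrolled, and if anything suggests that lack of internet is not a bar to entry. Health-trainer contact may be by telephone (section 8), and the Gantt chart lists the purchase of tablets. No passage says such patients are to be recorded as ineligible.

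**Conclusion.** The clause confounds eligibility with uptake, both of which feed primary outcomes, and it can inflate recruited/eligible. At half coding, true uptake of 20% to 70% reads as 33% to 82%: too high, but still tracking the truth.

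It is tempting to go further and say that the recruitment rate will be 100% whatever the true uptake. That needs two things: a denominator of eligible patients, which the protocol does not state, and every decliner coded under this clause, which section 7.3 does not require. On a screened denominator the recruitment rate does not change, although the eligibility rate still absorbs the refusals.

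The direction of the distortion follows from the protocol's own text. Its size rests on assumed values of u and f, and the screened-based eligibility figures rest also on the assumed 50%. Entry to the trial, randomisation and outcomes after entry are not affected.

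**What to change.** Remove "inability or unwillingness to undertake the commitments of the study" from the exclusion criteria in section 7.1 and keep the comorbidity clause in the same bullet. Log patients who meet the remaining criteria but do not enter as *eligible, declined* or *eligible, unable*, each with the reason. Report recruitment as randomised/eligible alongside randomised/screened.

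The change should precede screening: a log that codes refusals as exclusions without reasons cannot be separated afterwards. The cost is a one-line amendment, two screening-log codes and a stated recruitment rate that will look less favourable. Nothing is lost in control over entry, since consent under section 7.4 still governs it.
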